**Fig 1: Study outline**

Vaccination with influenza virus will be given during week 10 of the intervention and blood samples (80mL) taken 7 and 14 days post vaccination. These will be used to determine selenium supplementation-induced changes in mucosal and systemic humoral and cellular immune responses.

# 5.0 Recruitment Strategy

The study population will consist of six groups of apparently healthy 50-64y old men and women (n=24 per group) with low plasma (or serum) selenium. The volunteers will be recruited until 144have completed the study. Experience has shown that the drop out rate for these types of study is 25%. If a greater drop out rate occurs recruitment will be reviewed.

Advertisements (annex 3) will be placed around the Norwich Research Park (University of East Anglia (UEA), John Innes Centre (JIC), and IFR, in the HNU news letter (which is sent to all volunteers on the HNU volunteer database) in the local press and other suitable locations for example, supermarkets, social clubs, church news letters and golf clubs, gymnasiums and leisure facilities within the local area (40 mile radius). As in the past we will also obtain radio coverage and place advertisements (Annex 17 and 18) in the press to raise local awareness of the project if need be. The posters advertising this study will also be supplied with business cards or other suitable appendages to the poster in order to facilitate volunteer recruitment.

Apparently healthy volunteers from the HNU volunteer database, who meet the basic inclusion criteria, will be sent a letter of invitation (annex 2) to participate in the study. This will be supported by the volunteer information sheet (annex 4). Included will be a response slip and pre-paid envelope for returning the slip if they are interested and wish for further information. The HNU database has approximately 383 people between the ages of 50 and 64 years who are willing to participate in dietary intervention studies. It is known that at least 278 of these are non-smokers, and contact will made with these individuals.

Advertisements will also be placed on appropriate noticeboards in the Norfolk & Norwich University Hospital and on the NNUH intranet. Approaches will be made to GP practices via the Primary Care Research Network. In this instance, the GP will send out letters of invitation to individuals who meet the basic inclusion criteria. This will be supported by the volunteer information sheet and a response slip and pre-paid envelope for returning the slip directly to IFR if they are interested and wish for further information.

### 5.1 Basic Inclusion Criteria

- Men and women, age 50-64,
- Plasma selenium level is <1.2µmol/L (<95µg/L)

### 5.2 Basic Exclusion Criteria

- Elevated blood pressure measurements (<90/50 or <95/50 if symptomatic or >160/100).
- BMI <18.5 or >35
- Results of the clinical screening which are judged by the HNU Medical advisor to be indicative of a health problem and could compromise the well-being of the volunteer if they participated, or which would affect the data.
- Smokers
- Diagnosed with Gastrointestinal disease (excluding hiatus hernia unless symptomatic or study intervention/procedure is contraindicated) for which they have been taking prescription drugs on a chronic basis.
- Diagnosed with a long-term illness requiring active treatment, e.g. diabetes, cancer, cardiovascular disease.
- On regularly prescribed medication known to have a profound effect on the immune function
- Regularly using antacids and laxatives (at least once a week)
- sufferers of Hay-fever taking regular steroid medication
- Unwillingness to discontinue dietary (other than vitamins and minerals) or herbal supplements less than one month prior to the start of the study and for the duration of the study
- Blood donation within 16 weeks of the first study sample and who intend to donate blood less than 16 weeks after the last study sample
- Antibiotic use within four weeks prior to starting the study
- Those who receive or plan to receive any other type of immunisation during the study period
- Those who have received an immunisation within 6months of the start of the study
- Intention to go on holiday/trips for more than 2 weeks during the twelve week intervention
- Those planning a holiday/trip that requires immunisation during the twelve week intervention period
- Parallel participation in another research project which involves dietary intervention or sampling of biological fluids/materials
- Allergic to eggs or egg products
- Allergic to chicken protein
- Allergic to the antibiotic Gentamicin
- A history of Guillain-Barré syndrome

(There is a one in **one million chance (0.000001%)** of volunteers developing the Guillain Barré syndrome on administration of the flu vaccine. It is an acute disease of peripheral nervous system in which the nerves in the arms and legs become inflamed and stop working).

- Those who are offered a free flu vaccination because of a particular medical condition
- Healthcare workers who would receive a free NHS vaccination if their study vaccination would fall outside the NHS normal period (July-December)

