Dietary selenium is mainly present in organic complexes, such as selenomethionine (SeMet) found in cereals and plant foods, and Se- methylselenocysteine (SeMC) in selenium -accumulator plants such as onions and brassica vegetables, with smaller quantities of inorganic selenium derived from animal-based foods and dietary supplements (Combs, 2001). The metabolism and bioactivity of selenium is dependent on its chemical form: inorganic selenium can be used directly for the synthesis of GPx and other selenoproteins whereas selenomethionine is initially incorporated into tissue proteins, and only released for selenoprotein synthesis after further metabolism to selenide and selenocysteine (Reilly, 1996). The bioactivity of dietary selenium is related to its chemical form; SeMC has been identified as the most potent form of selenium in terms of protection against cancer possibly because, unlike SeMet which is incorporated non-specifically into proteins (Whanger, 2004), it can be converted directly into methyl selenol (Ca et al, 1995), a bioactive substance associated with cancer prevention (Ip & Ganther, 1996).

Recent epidemiological data from a pooled analysis of three clinical trials showed that individuals whose blood selenium values were in the highest quartile had a statistically significant lower risk (OR=0.66) of developing a colorectal adenoma (a pre-cancerous lesion) compared with individuals in the lowest quartile. These studies, therefore, suggest a mechanism for the decreased risk of colon cancer with selenium in which aberrant, age-related CpG island methylation is decreased by the inhibition of DNMT expression and activity. This study gives a unique opportunity to investigate the effect of selenium supplementation using recently developed techniques for the sensitive and accurate quantification of CpG island methylation in exfoliated colon cells present in faeces.

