Intakes of selenium in the UK have fallen from a mean of 60μg/day in 1974 to 30-40μg/day in recent years (Ysart et al, 1999) mainly due to the replacement of Canadian wheat (high in selenium) with European wheat (low in selenium); this has resulted in a fall in the mean plasma selenium concentration (Rayman, 1997). One of the proposed consequences of marginal selenium status is impaired immune function. As people age, they are more prone to infections and tumours and this is, at least in part, related to a decline in immune function. One effect of ageing on T lymphocytes is a shift towards a T-helper 2 (Th2) response during an infection, which means a reduced production of Th1 cytokines such as interleukin-2 (IL-2) and interferon-gamma (IFN-) (Cakman et al, 1996). In addition, natural killer (NK) cells, responsible for recognising and killing tumour and virally infected cells, exhibit an age-associated decline in activity, particularly in their ability to proliferate and to kill NK-resistant cell lines in response to IL-2 stimulation (Solano et al, 1999). As a direct consequence of this age-related decline of immune effectiveness, infectious diseases remain a significant cause of morbidity and mortality in the elderly. In particular, influenza virus is a globally very important contagion for the elderly (Nicholson et al, 2003) and few other diseases exert such huge toll in terms of suffering, medical consultation, hospital admission and economic loss (CDC-USA, 2003; Thompson et al, 2003).

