The project will consist of a placebo controlled selenium supplementation study and a dietary intervention with un-enriched and selenium enriched onions. In a parallel group design, subjects will be given either one of three doses of Se-yeast (50, 100 or 200μg selenium/day) or a placebo per day or selenium enriched or un-enriched onions (in the form of test meals) for 12 weeks (Figure 1). The study will allow us to investigate the effects of increasing the intake of dietary selenium as SeMet (found in the tablets) or SeMC (which will be the predominant form in the onions). Selenium supplementation studies using selenite have shown that 50 or 100μg/day selenium significantly increased plasma selenium concentration over a period of 6 weeks, at which point a plateau is reached (Broome et al, 2004). However, the intervention will be carried on for longer because we expect the response from Se-yeast to take longer. Outcome measures will include cellular and humoral immune responses to influenza vaccine (looking at the magnitude and the quality of this response; the up regulation of the immune response may or may not be related to viral clearance, as we are using a killed virus, but this will not be addressed in this study), changes in serum/plasma selenium concentration, selected selenoproteins, and expression of selenium -responsive genes and associated proteins. At IFR, we are currently investigating the effect of selenium form and dose on global gene expression in cell culture studies (micro array data), and have identified several selenium -responsive genes; quantitative RT-PCR (Taqman) analysis of mRNA from one gene (selenoprotein W1) demonstrated a linear dose-response within the physiological range of selenium ([name], unpublished). Results from our cell culture studies will indicate which genes and proteins to investigate in the human intervention study.

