**6.53 Compliance**

Meals will be provided and frequent contact with volunteers maintained during the intervention to check consumption of meals. The volunteers will be encouraged to inform us if they are not consuming the whole test meal. Volunteers will be given slightly more tablets than they will need in the blister packs. When the volunteers are invited back for their fasted blood in week six, they will be encouraged to bring the remainder of their blister pack so that we can issue a new set for the next six weeks and count the number of capsules they have consumed from the first set. A 24h urine sample will be collected midway through the intervention as selenium excretion is a good indicator of selenium intake. Serum/plasma selenium concentration will also be used as a check on compliance treatment.

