# 7.0 Statistical Analysis

Power calculations were done so that, out of the six study groups, a difference of 1 standard deviation in response variable between the minimum and maximum responding groups would be reliably detected. For example, for plasma selenium, previous studies (Shortt et al, 1997) suggest that the population standard deviation is 11.7, and so our sample sizes are designed to give an 80% chance of detecting a range of plasma selenium between the six groups of 11.7. For antibody secreting cells/500,000 lymphocytes and specific serum antibody (both at day 7 post-vaccination) the corresponding standard deviations are 76 and 19 respectively (Cox et al, 1999).

The power calculations also assumed that any effect of selenium supplementation would be proportional to the amount of supplementation, with enriched onions being equivalent to a supplementation of 50µg/day selenium and the un-enriched onions equivalent to no supplementation.

The power calculations were also based on the assumption that the data would be analysed using a one-way ANOVA model, the grouping having six levels (control, 50µg/day selenium, 100µg/day selenium, 200µg/day selenium, enriched onions, non-enriched onions). In order to be able to detect a range of 1 standard deviation between the groups with a power of 80%, a sample size of 144 (or 24 in each group) is sufficient. This allows for a drop-out rate of 25%, or in other words, finishing with 18 subjects in each group.

In the unlikely event of there being a year effect, and thus the two onion groups (but not the control and supplementation groups) being potentially compromised,24 subjects in each of the remaining 4 groups gives a power of 80% of detecting a range of 1 standard deviation in the response variable. This is based on using a two-way ANOVA model to analyse the data, with a three level year effect and a four level group effect (control, 50µg/d Se, 100µg/d Se, 200µg/d Se). It is important to stress however that we are aiming to recruit the full complement of 24 volunteers without the drop out rate of 25% as we feel there is a greater chance of compliance with the supplementation intervention.

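### The supplement exclusion exempts vitamins and minerals with no exception for selenium, so off-study use of the substance under test is permitted throughout the trial

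*Protocol*

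**What the plan says.** Section 5.2 (Basic Exclusion Criteria) lists as grounds for exclusion "Unwillingness to discontinue dietary (other than vitamins and minerals) or herbal supplements less than one month prior to the start of the study", continuing "and for the duration of the study". Vitamins and minerals are therefore outside the requirement to stop, both before entry and during the intervention.

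The study exposure is "one of three doses of Se-yeast (50, 100 or 200μg selenium/day) or a placebo per day", with two onion groups alongside: enriched onions equivalent to 50 µg/day, and un-enriched onions providing less than 1 µg/day (sections 2.0 and 6.2). Section 2.0 puts UK selenium intake at "30-40μg/day in recent years" and describes "smaller quantities of inorganic selenium derived from animal-based foods and dietary supplements" as part of the dietary supply.

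Two provisions bear on selenium from other sources:

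- Section 5.1 requires plasma selenium below 1.2 µmol/L (95 µg/L), measured at screening (section 5.4).
- Section 6.53 uses a 24-hour urine collection midway through the intervention and states that "Serum/plasma selenium concentration will also be used as a check on compliance treatment".

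Section 7.0 bases the power calculation on the assumption that "any effect of selenium supplementation would be proportional to the amount of supplementation", with un-enriched onions counted as no supplementation.

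**The concern.** The aim in section 1.0 is the relation between dose and form of selenium and immune function. The exemption covers the class of product to which selenium belongs. A volunteer on placebo could take a selenium-containing multivitamin or mineral product for the whole study without breaching the protocol.

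Three things are at stake:

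- **Dose contrast.** The steps between arms are 50 to 100 µg/day, on a background intake of 30-40 µg/day. An off-study product of similar size would put a placebo volunteer's added intake at the level of the lowest-dose arm.
- **Form contrast.** The trial compares selenomethionine (tablets) with Se-methylselenocysteine (onions). Section 2.0 names supplements as a source of inorganic selenium, so their use could bring a third form into either arm.
- **Compliance markers.** A raised plasma or urine selenium in an active arm could come from the study product or from elsewhere, so off-study use can hide missed tablets or meals.

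**Working it through.** **Step 1: what the text permits.** Section 5.2 exempts vitamins and minerals, writes no exception for selenium, and covers the whole study. Sections 6.1, 6.2, 6.51 and 6.52 govern only the study tablets and meals. The medication declaration in section 5.4 concerns medication. Nothing in the protocol text shown restricts off-study selenium.

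**Step 2: whether the safeguards close the gap.** The limit in section 5.1 is applied at screening. It can exclude a user whose status is already high, but it does not prevent someone below the limit from continuing or starting a product afterwards. The markers in section 6.53 detect selenium, not its source. In the placebo and un-enriched onion arms an unexpected rise would be visible; in the active arms it could not be attributed.

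**Step 3: size under the protocol's proportional-effect assumption.** Inputs from section 7.0: six groups, a range of 1 SD, effect proportional to dose, and 24 per group recruited or 18 after drop-out. Alpha is not stated; I assume 0.05.

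- Group means in SD units, dose/200: placebo 0; 50 µg 0.25; 100 µg 0.5; 200 µg 1; enriched onions 0.25; un-enriched onions 0.
- Mean = 2/6 = 0.333. Sum of squared deviations = 1.375 − 6 × 0.333² = 0.708.
- Noncentrality λ = n × 0.708: 12.75 at n = 18 and 17.0 at n = 24.
- Power of the one-way F-test: 0.772 at 18 per group (the protocol states 80%) and 0.897 at 24.

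Now let a share q in every arm take d µg/day off-study, with additive effects. All group means shift equally, so the contrasts are unchanged. The within-group variance becomes 1 + q(1−q)(d/200)², and λ is divided by that amount. Both q and d are my assumptions.

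| q | d (µg/day) | Variance | Power, n = 18 | Power, n = 24 |
| --- | --- | --- | --- | --- |
| 0 | – | 1 | 0.772 | 0.897 |
| 10% | 50 | 1.006 | 0.769 | 0.895 |
| 10% | 100 | 1.023 | 0.761 | 0.890 |
| 30% | 50 | 1.013 | 0.766 | 0.893 |
| 30% | 100 | 1.053 | 0.747 | 0.879 |
| 30% | 200 | 1.210 | 0.677 | 0.823 |

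For 50-100 µg/day the loss is about 0 to 3 percentage points.

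**Step 4: size if users are saturated.** Suppose instead that a share q is already at a plateau and shows no further response to the study product. Every mean is then multiplied by (1−q), and λ by (1−q)².

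| q | Power, n = 18 | Power, n = 24 |
| --- | --- | --- |
| 0 | 0.772 | 0.897 |
| 10% | 0.666 | 0.814 |
| 20% | 0.548 | 0.700 |
| 30% | 0.427 | 0.565 |

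This departs from the proportional-effect assumption in section 7.0, and the documents give no value for q.

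**The case against.** The best defence is that selenium status is actively screened. Section 5.4 treats the selenium measurement as the major part of screening. A habitual user is measured with the supplement on board, so anyone it has lifted above 95 µg/L is excluded, and those who pass have low status despite it. The saturation scenario therefore needs users who are saturated below the limit, or use that begins after screening. This stands, and it is why the second table should not be read as the expected loss.

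It can also be said that background diet is equally uncontrolled, that arm labels denote selenium added by the study, and that randomisation balances off-study use in expectation. This also stands. A reader might infer that the placebo comparison is systematically biased, or that the arm labels are simply wrong; the documents support neither. Section 2.0 speaks only of smaller quantities of inorganic selenium from supplements and animal foods together, and compliance is also checked by a tablet count at week 6.

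Finally, the screening questionnaire and the volunteer information sheet are annexes that are not shown. They may ask about supplements or restrict them. A restriction there would conflict with section 5.2 as written, and the two would need reconciling.

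None of this alters what section 5.2 permits during the 12 weeks.

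**Conclusion.** The point holds as a design weakness: the eligibility rule allows uncontrolled intake of the test substance, and no other provision shown prevents it. The harm is a blurred dose and form contrast, some added variance and weaker compliance markers. On the protocol's proportional-effect assumption the power cost is small, about 0 to 3 points if 10-30% of volunteers take 50-100 µg/day. A larger loss requires saturated users. These figures assume alpha 0.05 and usage rates that the documents do not supply.

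A reader might also infer that the one-month timing clause helps to let selenium in. It does not: vitamins and minerals are exempt, so the clause governs only the other dietary and herbal supplements. For those it is a separate drafting fault. Read literally it sets a maximum interval, so that stopping shortly before entry would satisfy it, whereas a wash-out needs a minimum.

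**What to change.** In section 5.2, limit the vitamin and mineral exemption to products that contain no selenium. Record supplement use, with product name, at screening and at each existing blood visit (weeks 0, 6, 10, 11 and 12), so that off-study selenium is a documented deviation that can be examined in the analysis. Check that the screening questionnaire and the volunteer information sheet say the same.

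As a separate wording correction for the non-exempt supplements, express the one-month period as a minimum interval before the start of the study.

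The cost is one revised eligibility sentence, one question at visits already planned, and a slightly smaller recruitment pool. Use that was never asked about cannot be reconstructed afterwards, so the change belongs before recruitment.

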In order to allow for the unlikely possibility of a year effect the control group and each of the three selenium supplementation groups will be evenly and randomly spread over the three years. Unfortunately due to time constraints, this is not possible with the onion groups which will be evenly and randomly spread over only two of the years (i.e. half in each year). The two onion groups will also be able to be analysed separately, but with a reduced power of 18 subjects per group gives a power of 80% of detecting a difference in response variable of 1 standard deviation. This is quite a large effect of the enriched onions, given that they are only “equivalent” to a selenium dose of 50µg/day. This is based on a 25% drop out rate expected for the onion intervention study.

The data would be initially analysed using an ANOVA model to test for differences in end-points between the groups. If the required data assumptions for this model are not met (e.g. normality), then data transformations and/or non-parametric methods will be employed. A repeated measures analysis using all 5 data points per subject will also be used, although it is the end-point (week 12) that is of primary interest.

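### The 6-month immunisation rule admits most volunteers given influenza vaccine the previous autumn, and no rule expressly bars re-enrolment in a later year; both can be closed cheaply at entry

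*Protocol*

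**What the plan says.** Three rules in protocol section 5.2 bear on earlier exposure to vaccine or to the study.

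- Past immunisation: the protocol excludes "Those who have received an immunisation within 6months of the start of the study".
- Immunisation during the study: it excludes "Those who receive or plan to receive any other type of immunisation during the study period".
- Participation: it excludes "Parallel participation in another research project which involves dietary intervention or sampling of biological fluids/materials".

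Two further rules remove some people likely to have been vaccinated before. One excludes "Those who are offered a free flu vaccination because of a particular medical condition". The other excludes healthcare workers, but only when their study vaccination would fall outside the normal NHS period. Section 4.1 adds that healthcare workers and people offered free NHS vaccine cannot take part in December to February.

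On timing, section 6.1 has the first volunteers of each project year starting in July, with first vaccinations in the second half of September. The vaccination period runs to February and may be extended to April. Table 1 spreads tablet recruitment over three project years and onion recruitment over the last two.

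Sections 6.0 and 6.4 stratify allocation by sex only. Section 7.0 states: "The data would be initially analysed using an ANOVA model to test for differences in end-points between the groups". It names week 12 as the time point of main interest and adds a repeated-measures analysis of all five samples.

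**The concern.** The rule on past immunisation is general, while the study outcome is specific to influenza vaccine. A 6-month window removes people vaccinated recently, but it does not separate those who had the previous season's influenza vaccine from those who did not. Neither the stratification nor the stated ANOVA takes account of that history. Such volunteers could well come forward: section 5.0 says "Advertisements will also be placed on appropriate noticeboards in the Norfolk & Norwich University Hospital and on the NNUH intranet", and the healthcare-worker exclusion is conditional on timing.

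If vaccination history affects the immune response, it adds between-subject variance to every immune comparison. A model can remove this only if the history is recorded at entry.

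The participation rule leaves a second, smaller gap. Taking part in this same trial a year earlier is neither parallel nor another project. A returner would contribute two records to an ANOVA that treats records as independent, and would bring earlier study vaccine, and possibly earlier selenium, into the second period.

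**Working it through.** **1. Calendar check of the 6-month rule.** The inputs are July starts and the September to February vaccination period, extendable to April (section 6.1). Six months is taken as 183 days.

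- Earliest start: 1 July 2006 minus 183 days = 30 December 2005.
- Vaccinated 20 September 2005: 9.3 months before a 1 July start and 14.8 months before a 15 December start. Admitted throughout.
- Vaccinated 31 December 2005: on the boundary at 1 July (6.0 months, just excluded), admitted at 1 August (7.0).
- Vaccinated 28 February 2006: excluded at 1 July and 1 August (4.0 and 5.1 months), admitted at 1 September (6.1).
- Vaccinated 30 April 2006: excluded at 1 July, 1 August and 1 September, admitted at 1 November (6.1).

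The rule therefore admits almost all autumn vaccinees of the season before. It excludes late-season vaccinees who start soon afterwards.

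**2. Calendar check of re-enrolment.** Take year-1 study vaccinations as 15 September 2005 to 28 February 2006. Adding 183 days gives 17 March to 30 August 2006. A year-1 volunteer could thus clear the immunisation rule in time for year 2.

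**3. The plan's own power figure, for scale.** Section 7.0 claims 80% power for a range of 1 SD over six groups, with effects proportional to dose and 18 completers per group. The group means in SD units are 0, 0.25, 0.5, 1, 0.25 and 0 (placebo, 50, 100, 200, enriched onions, un-enriched onions). Their mean is 0.333 and their sum of squared deviations is 0.708.

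- Noncentrality: λ = n × 0.708 / residual variance.
- n = 18, variance 1: λ = 12.75 and power = 77.2% (5% level, 5 and 102 df).
- n = 24, variance 1: λ = 17.0 and power = 89.7%.

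The small gap between 77.2% and 80% is not the issue here.

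**4. Possible gain from adjustment.** If a share q of volunteers had the previous season's vaccine and their response differs by d SD, the share of variance explained is q(1 − q)d². The protocol gives neither q nor d. *Assumption:* q = 0.2 to 0.5 and d = 0.5 to 1.

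- Low end: 0.2 × 0.8 × 0.25 = 0.04.
- High end: 0.5 × 0.5 × 1 = 0.25.

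This treats the planning SD as already containing the variation, so adjustment leaves a residual variance of 0.96 to 0.75.

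| Per group | Unadjusted | Residual variance 0.96 | Residual variance 0.75 |
|---|---|---|---|
| 18 | 77.2% | 79.1% | 89.2% |
| 24 | 89.7% | 91.0% | 96.8% |

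**The case against.** A reader might infer that the immune outcomes will mix previously vaccinated and unvaccinated responders, and that some people will be counted twice. The protocol supports neither as a fact.

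- **Double counting rests on silence.** Nothing plans re-enrolment. Section 2.0 describes a parallel-group design, and section 6.1 says that completing the 12 weeks ends the volunteer's participation. A returner would also need plasma selenium below 1.2 µmol/L again. Section 5.0 describes a newsletter and invitation letters to the unit's database, but does not say that mailings are repeated each year or reach earlier participants. Any count of returners would be invented. It remains true that no eligibility rule forbids a second enrolment.
- **Bias is not shown.** Among groups randomised at the same time, vaccination history balances in expectation. Returners could fall unevenly between onion and tablet groups, because they can occur only in years 2 and 3, which hold all onion volunteers but two thirds of tablet volunteers. That would need re-enrolment on a scale nothing in the protocol suggests.
- **Earlier immunity is partly measured.** Blood for immune assays is drawn before vaccination at weeks 0 and 10, and baseline saliva is tested for influenza antibody. This can recover part of the variance, so a history question adds to these measurements and is not the only remedy.
- **The question may already be asked.** Annex 7, the screening questionnaire, is not shown, and applying the 6-month rule requires asking about past immunisation. Covariates are also commonly left to an SAP. However, an SAP can adjust only for history that was collected at entry.
- **The assumed share may be high.** The medical-condition and healthcare-worker exclusions shrink the group of earlier vaccinees. The top of the gain needs both assumptions at their extremes. At 24 per group, which section 7.0 says is the aim, the gain is at most about 7 points.

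**Conclusion.** The point holds as a cheap improvement to eligibility and data collection. It is not a demonstrated flaw in the comparison. Calendar arithmetic alone shows that the rule admits most previous-autumn influenza vaccinees, and the wording of section 5.2 shows that later re-enrolment is not expressly barred. How often either would occur cannot be known from the protocol.

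The expected consequence is extra variance in the immune outcomes. The power gain from adjusting is 2 to 12 points at 18 per group and 1 to 7 points at 24. These figures depend on the assumed share and effect of prior vaccination, and on the planning SD already including that variation. They take no credit for what the pre-vaccination samples would explain, so the further gain once those are in the model would probably be smaller.

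**What to change.** 1. Add previous participation in this study to the exclusions in section 5.2.
2. Record at screening, as yes or no, whether influenza vaccine was received in the preceding season, if annex 7 does not already ask. The 6-month rule can stay as it is.
3. Include that factor in the immune-outcome models, alongside the pre-vaccination measurement already collected.

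The cost is one exclusion line, at most one questionnaire item and one model term (one degree of freedom). Any earlier participants willing to return would be lost to recruitment.
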